## Abstract

**Background:**

In the last few years, new noninvasive strategies have emerged as rehabilitative treatments for patients with stroke. Action observation treatment (AOT) is a rehabilitation approach based on the properties of the mirror neuron system with a positive impact on modifying cortical activation patterns and improving the upper limb kinematics. AOT involves the dynamic process of observing purposeful actions with the intention of imitating and then practicing those actions. In recent years, several clinical studies suggested the effectiveness of AOT in patients with stroke to improve motor recovery and autonomy in activities of daily living. However, a deeper knowledge of the behavior of the sensorimotor cortex during AOT seems to be essential.

**Objective:**

The aim of this clinical trial, conducted in 2 neurorehabilitation centers and in patients’ homes, is to investigate the effectiveness of AOT in patients with stroke, confirming the translational power of a tailored treatment. Particular emphasis will be placed on the predictive value of neurophysiological biomarkers. In addition, the feasibility and impact of a home-based AOT program will be investigated.

**Methods:**

A 3-arm, assessor-blinded, randomized controlled trial will be performed by enrolling patients with stroke in the chronic stage. A total of 60 participants will be randomly allocated to receive 15 sessions of AOT with different protocols (AOT at the hospital, AOT at home, and sham AOT), 3 sessions per week. The primary outcome will be assessed using the Fugl-Meyer Assessment-Upper Extremity scores. Secondary outcomes will be clinical, biomechanical, and neurophysiological assessment.

**Results:**

The study protocol is part of a project (project code GR-2016–02361678) approved and funded by the Italian Ministry of Health. The study began with the recruitment phase in January 2022, and enrollment was expected to end in October 2022. Recruitment is now closed (December 2022). The results of this study are expected to be published in spring 2023. Upon completion of the analyses, we will examine the preliminary effectiveness of the intervention and neurophysiological outcomes.

**Conclusions:**

This study will be used to evaluate the effectiveness of 2 different AOT scenarios (ie, AOT at the hospital and AOT at home) in patients with chronic stroke and to assess the predictive value of neurophysiological biomarkers. Specifically, we will attempt to induce the functional modification of the cortical components by exploiting the features of the mirror neuron system, demonstrating relevant clinical, kinematic, and neurophysiological changes after AOT. With our study, we also want to provide, for the first time in Italy, the AOT home-based program while assessing its feasibility and impact.

**Trial Registration:**

ClinicalTrials.gov NCT04047134; https://clinicaltrials.gov/ct2/show/NCT04047134

**International Registered Report Identifier (IRRID):**

DERR1-10.2196/42094

## Introduction

### Background

Stroke is a leading cause of death and one of the most common causes of long-term disability that interferes with good quality of life [1]. Currently, one of the major components of rehabilitation interventions is focused on disability reduction to achieve the functional motor goal [2]. In the last few years, to improve activities of daily living (ADL), new noninvasive strategies that have emerged as rehabilitative treatments have been added to conventional motor rehabilitation programs [3,4].

One such noninvasive strategy is the action observation treatment (AOT), supported by results collected through randomized controlled trials [5-10]. This new rehabilitation approach is based on the network properties of the mirror neuron system (MNS) [11-13]. AOT involves the dynamic process of observing purposeful actions with the intention of imitating and then practicing those actions.

Extensive research over the last 20 years on human MNS [14-16] showed its importance not only in action recognition [17] but also in understanding action intentions and other important social cognitive aspects [14,16]. Moreover, higher activation of temporoparietal networks was found when a goal-directed action was observed [18]. Enabling the patients to acquire new skills and potentially relearn movement patterns, AOT is involved in the motor learning process and could be a helpful adjunctive treatment to conventional therapy in upper limb motor rehabilitation. Indeed, AOT seems to be a useful rehabilitation strategy in addition to physical therapy for improving upper limb functions, especially in daily activities after stroke [19,20], alone or in association with motor imagery [21]. Finally, because it is also recruited in the damaged brain [22,23], the MNS is demonstrated to provide remarkable rehabilitative outcomes [7,24-27].

On the basis of the MNS properties able to activate the sensory-motor system through the observation of actions as well as the execution of the same actions, the AOT is proving to be an innovative rehabilitative approach for recovery of patients with stroke in chronic stage with upper limb impairment; several findings are present in scientific literature [5,23,27-31].

On the basis of these results, several clinical studies have been published in recent years, suggesting the effectiveness of AOT in improving motor recovery and autonomy in ADL [19,20,24,32]. However, a deeper knowledge of the behavior of the sensorimotor cortex during AOT seems to be essential. Recent studies have investigated cortical responses during the visualization of standardized actions by using 4 biomarkers primarily: related desynchronization and synchronization of alpha and beta rhythms (event-related desynchronization [ERD] and event-related synchronization [ERS]), beta brain coherence, and mu rhythm suppression [33-36].

In our previous work, we administered AOT treatment to a group of patients with stroke and observed the predictive value of ERD of electroencephalography (EEG) alpha rhythm (ie, 8-13 Hz) during rehabilitation tasks and at the end of the treatment, as a sign of neural plasticity. In addition, increased functional dexterity was found in patients with stroke in the subacute stage that had AOT compared with their peers who underwent a control treatment [8].

Recently, our research group conducted a pilot study to assess which type of ADL visual stimulus was the most effective in inducing motor excitability during action observation. EEG signals were recorded in 20 patients with stroke in chronic stage during the observation of task-oriented upper limb tasks (including self-care and feeding actions) and nonfinalized actions. The comparison of EEG rhythms between the 2 groups of motor actions (ie, task-oriented and non–task-oriented) revealed that an increased suppression of mu and beta bands occurred during the observation of the former category [37].

The procedures described in this protocol, including recruitment, assessments, and visual stimuli for motor action, have been tested in a single-group uncontrolled feasibility study. Preliminary analysis from a qualitative observation of a few collected data by using the proposed protocol showed desynchronization effects of all cerebral rhythms (especially of the beta rhythm) after the AOT treatment (ie, pretest vs posttest assessment). In addition, a few patients had alpha and beta rhythm desynchronization compared with a group of healthy participants.

The encouraging results obtained from clinical outcomes were confirmed by studies that included instrumental assessments, among others: AOT has an additional positive impact on modifying cortical activation patterns [9,26,38] and in improving upper limb kinematics [39].

Furthermore, in Italy, to the best of our knowledge, no evidence has been found related to the effectiveness of home-based AOT programs compared with the same AOT performed in the hospital.

According to the inspiring results reported in the literature, AOT rehabilitative treatment exemplifies a translational step from neuroscience to clinical rehabilitation applications.

### Aims

The project aims to achieve the following objectives: (1) induce functional modification of the cortical components underpinning the action organization, exploiting the peculiar features of the MNS and demonstrating the relevant clinical, kinematic, and neurophysiological changes after AOT—in particular, the analysis of the AOT effectiveness will also consider the predictive value of neurophysiological biomarkers; and (2) provide the home-based AOT program, to the best of our knowledge, for the first time in Italy, thereby rendering evidence-based considerations regarding the feasibility and impact of our home-based AOT program for future systematic application of the approach.

## Methods

### Overview

A randomized, parallel-arm, controlled, outcome measurer–blinded, and multicenter clinical trial conducted in 2 neurorehabilitation centers in Italy aims to investigate the effectiveness of AOT in patients with chronic stroke (ie, >6 months from the first event) using quantitative EEG biomarkers, confirming the translational power of a tailored treatment.

A total of 60 individuals who have been enrolled will be randomized to the experimental group in hospital (EG@Hosp), experimental group at home (EG@Home), or control group (CG) in a 1:1:1 ratio.

The EG@Hosp will observe and execute ADL that are task-oriented actions (AOT protocol); the EG@Home will observe and perform the same ADL at home (AOT protocol at home); and the CG will not observe any motor task videos (but will watch video only on landscapes and historical issues), and after verbal instructions, they will perform the same actions observed by the other 2 groups.

After completing the patient screening, randomization will be performed before the first treatment session (T0). At baseline (T0), midintervention (after the 7th session; T1), and after the intervention (15th session or 5th week; T2), outcomes (ie, clinical scales, EEG and electromyography [EMG] signals, and kinematic parameters) will be assessed to evaluate impairment and functional abilities.

For each group, the total duration of the intervention will be 5 weeks (3 times a week) for a total of 15 sessions. After the end of the intervention, a 2-month follow-up assessment period (T3) will be scheduled to assess the maintenance and long-term effects.

The primary outcome assessed at T2 will be assessed by the Fugl-Meyer Assessment-Upper Extremity (FMA-UE) scores.

The trials will be performed at 2 neurorehabilitation centers in Italy: IRCCS San Raffaele Roma Hospital in Rome and at Casa di Cura del Policlinico Hospital in Milan.

All the data will be recorded in electronic case report forms through the REDCap (Research Electronic Data Capture; Vanderbilt University) system, accessed on the web via the internet for data collection and management.

A specific route diagram is presented in Figure 1. The protocol for this study was developed in accordance with the Standard Protocol Items: Interventional Trial Recommendations guidelines (SPIRIT) [40].

**Figure 1 figure1:**
[figure not shown]
Flowchart of the proposed randomized controlled trial according to the Consolidated Standards of Reporting Trials. CG: control group; EG@Home: experimental group at home; EG@Hosp: experimental group in hospital.

### Study Population, Setting, and Recruitment

This study will be conducted in patients with chronic stroke. Between January 2022 and October 2022, a total of 60 outpatients or inpatients were recruited from the 2 centers mentioned earlier. The intervention will be provided in 2 different settings: rehabilitation centers (EG@Hosp and CG) and the patient’s home (EG@Home).

Patients will be included after signing a written informed consent form, provided the inclusion and exclusion criteria are met.

The schedule of enrollment, interventions, and assessments are presented in Figure 2.

**Figure 2 figure2:**
[figure not shown]
Standard Protocol Items: Interventional Trial Recommendations (SPIRIT) diagram describing schedule of enrollment, interventions, and assessments. *Only for experimental group at home intervention group. BBT: Box and Block Test; CG: control group; EEG: electroencephalography; EG@Home: experimental group at home; EG@Hosp: experimental group in hospital; EMG: electromyography; FAT: Frenchay arm test; FMA-UE: Fugl-Meyer Assessment-Upper Extremity; MAS: Modified Ashworth Scale; mBI: Modified Barthel Index; TAM: Technology Acceptance Model.

### Selection Criteria

The inclusion and exclusion criteria of participants is shown in Textbox 1.

Patients with intellectual disability or other serious pathological conditions (eg, aphasia and hemianopsia) that affect their ability to watch or understand the proposed video were excluded.

Participant inclusion and exclusion criteria.
**Inclusion criteria**
First ever unilateral ischemic stroke in the chronic stage (ie, the time elapsed from the event>6 months) provoked a clinically evident upper limb or hand deficit that affects the daily activitiesDiagnosis verified by brain imaging (magnetic resonance imaging)Aged 18-85 yearsCognitive function sufficient to understand the experimental instructions (Mini-Mental State Examination Score of≥24)Chedoke-McMaster Stroke Assessment Scale—arm-hand section score of>1
**Exclusion criteria**
Bilateral impairmentSevere sensory deficits in the paretic upper limbCognitive impairment or behavioral dysfunctionAny other neurological or orthopedic deficit that affects arm functionAny severe cardiovascular disease that can preclude interventionAny other current severe medical problemsRefusal or inability to provide informed consent

### Randomization

On the enrollment day, by using the electronic data capture system software (ie, REDCap) and the method of central stratified regional group randomization, the enrolled patients will be randomly allotted to one of the 3 groups (ie, EG@Hosp, EG@Home, and CG).

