### Sample Size

As the changes in the effects of upper limb AOT in patients with stroke on EEG biomarkers have not been previously investigated, we have estimated the sample size based on previously published studies [58,59], comparing AOT and conventional therapy. We estimated the sample size required to detect differences in the effects of “group”×“time” interactions on primary clinical outcome (FMA-UE).

For this outcome, an effect size of 0.495 [60,61] is expected based on previous studies. Given the expected effect size, a total sample size of 54 will be required for repeated ANOVA with a power of 0.8 and a 2-sided type-I error of 0.05 (number of groups=3 [ie, EG@Hosp, EG@Home, and CG]; number of measurements=3 [ie, T1, T2, and T3]). Therefore, when considering a dropout rate of 10%, we plan to recruit 20 participants for each group (a total of 60 participants) for this study.

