#### Analysis of the Effectiveness

Analysis of the primary outcome (ie, functionality of the affected upper extremity) will be performed using the per-protocol principle. Treatment effects will be compared using a 2-way repeated ANOVA for clinical measurements, considering “time” (3 levels: T0, T1, and T2) as a within-subject factor and “group” (3 levels: EG@Hosp, EG@Home, and CG) as a between-subject factor.

In addition, the percentage of participants who passed the minimal clinically important differences of the FMA-UE will be compared using chi-square tests between the 3 groups.

The mean power across the assessment “time” (ie, T0 and T2) related to the action observation condition will be implemented in a mixed-design ANOVA to evaluate significant changes. A separate ANOVA will be performed to assess power changes in the stimuli selection data, using “treatment” (ie, EG@Hosp vs EG@Home vs CG) as the between-subjects factor and action as the within-subjects factor. To assess the predictive value of biomarkers for AOT effectiveness, an analysis of covariance (ANCOVA) will be performed considering the clinical data as the dependent variable, the “group” as a fixed factor, and the biomarkers as covariates.

Subsequently, to evaluate kinematic parameters recovery, a mixed design ANOVA will be implemented with “time” and “treatment” as within- and between-subjects factors, respectively.

The level of significance will be set at *P*<.05. For post hoc comparisons, the level of significance will be set at *P*<.017 after Bonferroni adjustment (.05/n; the number of comparisons, n=3) for the comparison of interaction effects. Cohen *d* will be calculated to determine the effect size of the change in scores for the behavioral motor outcomes between the groups. Immediate training effects (data from T0-T2) and the durability of training effects (data from T2-T3) will be separately investigated using mixed effect models.

Clinical-neurophysiological correlations will also be analyzed: the correlation between the ERD and factors such as the clinical scale score will be studied. To evaluate the differences in trends related to the clinical evolution of the patients, we will define a new variable to group the participants according to the presence or absence of relevant clinical improvements. The relevant clinical improvement will be defined by a clinical specialist for this purpose.

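### Allocation is stratified by region, but no model whose factors are listed contains the stratification factor; the cost is negligible for the group × time interaction and modest for between-subject comparisons

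*Protocol article*

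**What the plan says.** - **Allocation.** The Randomization section assigns patients through REDCap by "the method of central stratified regional group randomization". It does not define the strata further.
- **Centres.** The Methods Overview states: "The trials will be performed at 2 neurorehabilitation centers in Italy". One is in Rome and the other in Milan.
- **Primary model.** Under Analysis of the Effectiveness: "Treatment effects will be compared using a 2-way repeated ANOVA for clinical measurements". Its factors are time ("3 levels: T0, T1, and T2) as a within-subject factor") and group ("3 levels: EG@Hosp, EG@Home, and CG) as a between-subject factor").
- **Other models with listed factors.** The same section gives a mixed-design ANOVA of EEG power over T0 and T2, a separate EEG ANOVA with treatment between and action within subjects, a kinematic ANOVA with time and treatment, and an ANCOVA of clinical data on group and biomarkers. None names centre or region.
- **Models without listed terms.** The mixed effect models for T0-T2 and T2-T3 are named, but their terms are not given.
- **Sizing.** The Sample Size section targets the group-by-time "interactions on primary clinical outcome (FMA-UE").

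**The concern.** A factor used to restrict the randomisation should normally appear in the analysis. Stratifying by centre balances the groups on centre, so centre differences do not contribute to the true variability of a group difference. A model without centre still counts them as error. The estimated standard error is then larger than the true one, and the test rejects less often than its nominal level. In a trial planned for 60 patients, with 54 expected to complete, avoidable loss of precision deserves a look. An analysis plan that is not shown could add detail, but here the factors and their levels are listed and the design factor is not among them. How much this costs depends on which effect is tested.

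**Working it through.** **1. The plan's own figure.** The Sample Size section states "an effect size of 0.495 [60,61] is expected based on previous studies" and "a total sample size of 54 will be required for repeated ANOVA with a power of 0.8 and a 2-sided type-I error of 0.05". Take 0.495 as Cohen's f (the metric is not named), with g = 3 groups, m = 3 visits and noncentrality λ = f²N.

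- df1 = (g−1)(m−1) = 4; df2 = (N−g)(m−1)
- N = 52: λ = 0.245 × 52 = 12.74, df2 = 98, power 0.81. N = 51 falls just short at 0.798.
- Three equal groups give N = 54: λ = 13.23, df2 = 102, power 0.825.
- 54/0.9 = 60.

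So 54 and 60 reproduce for the interaction under this reading, and neither depends on a centre term.

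**2. Interaction, constant centre difference.** The group × time test uses only within-patient contrasts between visits. Adding a constant to every visit of every patient at one centre leaves those contrasts unchanged. In one simulated data set the interaction p value was 0.0089 for centre shifts of 0, 0.5, 0.8 and 2 SD alike.

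**3. Single-visit contrast.** Assume two equal centres, balanced over groups, that differ by d within-centre SDs. Without centre in the model, the residual variance is multiplied by 1 + d²/4 and the SE by its square root:

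- d = 0.3: √1.0225 = 1.011
- d = 0.5: √1.0625 = 1.031
- d = 0.8: √1.16 = 1.077

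**4. Group main effect.** This test uses each patient's mean over three visits. With an assumed within-patient correlation of 0.5, that mean has variance (1 + 2 × 0.5)/3 = 2/3, so the error variance is multiplied by k = 1 + (d²/4)/(2/3). The nominal 5% critical value of F(2, 51) is 3.179, and the actual size is P(F > 3.179k).

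- d = 0.5: k = 1.094, size 0.038
- d = 0.8: k = 1.24, size 0.026

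**5. Simulation.** The setting is 54 patients, 9 per group per centre, three visits, correlation 0.5, and 20,000 runs per setting. The assumed treatment effect rises linearly from T0 to T2 in both experimental groups and gives about 80% interaction power. Each cell shows the model without, then with, centre and centre × time.

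| Assumed centre difference | Interaction power | Interaction size | Main-effect size | Main-effect power |
|---|---|---|---|---|
| None | 0.799 / 0.799 | 0.050 / 0.050 | 0.050 / 0.050 | 0.46 / 0.46 |
| Level, 0.5 SD | 0.800 / 0.799 | 0.052 / 0.051 | 0.038 / 0.050 | 0.41 / 0.46 |
| Level, 0.8 SD | 0.801 / 0.801 | 0.049 / 0.049 | 0.025 / 0.052 | 0.33 / 0.45 |
| Change by T2, 0.3 SD | 0.786 / 0.791 | 0.046 / 0.049 | 0.049 / 0.050 | 0.45 / 0.45 |
| Change by T2, 0.5 SD | 0.784 / 0.798 | 0.042 / 0.048 | 0.044 / 0.048 | 0.43 / 0.45 |

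The simulated main-effect sizes agree with step 4. The interaction gains about 0.5 and 1.4 points of power from the centre terms when change differs by centre, and nothing when only the level differs. The simulation standard error of a power near 0.8 is √(0.8 × 0.2/20,000) ≈ 0.3 points.

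**The case against.** The strongest reply is that the trial is sized on the interaction, where each patient serves as their own control. Stable differences between Rome and Milan drop out, and with complete data a centre main effect alone leaves that F test unchanged. The same holds for the time × treatment tests on EEG power and kinematics. The group main effect, which averages over baseline, is not the test that carries the trial. All of this stands.

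A reader might infer more than the documents support:

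- **That the primary test loses precision in general or runs clearly below 5%.** It does not. Without centre, the interaction size stayed between 0.042 and 0.052, and only centre-specific change moves it.
- **That EEG and kinematics suffer most because equipment differs by site.** The article allows 64 to 128 electrodes but never says that the number varies by centre, and a stable laboratory offset cancels from change over time.
- **That centre is absent from every analysis.** The T0-T2 and T2-T3 mixed effect models list no terms, and no EMG model is stated.
- **That region is certainly centre.** The article does not say so.

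The reply does not reach comparisons that are between subjects. These are a direct group contrast at T2, where the Overview places the primary outcome; the treatment effect in the EEG treatment × action ANOVA; and the biomarker ANCOVA if its outcome is a score at one visit. In the ANCOVA there is a further point: biomarkers are not randomised. If site affected both the EEG reading and the clinical score, stratified allocation would not protect the biomarker association, and a model without centre could not separate the two.

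**Conclusion.** The listed models do not follow the stated design, and this is a minor flaw. For the group × time interaction the loss runs from nothing, for a constant centre difference, to about 1.4 points of power if change by T2 differs between centres by 0.5 SD. For between-subject group comparisons it is larger: a single-visit SE about 1%, 3% or 8% too large at 0.3, 0.5 or 0.8 SD, and a main-effect test at about 3.8% or 2.5% instead of 5% at the latter two. Omitting the factor does not raise the false-positive rate of the group comparisons. The article gives no figures for centre differences or within-patient correlation, so every size here rests on the assumed values, on equal centres, and on reading region as centre.

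**What to change.** Before analysis, state what the REDCap strata are and add that factor as a fixed effect to the FMA-UE, EEG and kinematic models and the biomarker ANCOVA. In the repeated-measures models include its interaction with time as well, because the main effect alone does nothing for the group × time test. A baseline-adjusted comparison at T2 that includes centre would serve equally well for the primary outcome.

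With 54 completers and two centres, the between-subject error falls from 51 to 50 degrees of freedom and the interaction error from 102 to 100. In the simulation the added terms cost at most about 0.1 points of interaction power when centre did not affect change. No new data are needed, since the allocation is made in REDCap.

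This change does not alter the sample size.
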